### Data analysis

The intervention analyses will focus on two major questions: What aspects of Transfer does the values interventions positively influence? By what processes does the intervention work? We are primarily interested in investigating effects at the cluster-level, though will explore overall effects of the addition coaching-component on the entire sample and participant-level data in the qualitative processes described. The figure below presents a model of the analyses. Model A represents the total effect of values intervention versus control condition (implementation) (X) on Transfer (Y). Model B represents the direct effect of X on Y, and the indirect effect through the mediator (M), our psychological process variable (autonomy).

Model C is a multiple mediation model, and will allow us to test the extent that our intervention targets multiple process variables (*e*.*g*., value importance, value success, value commitment). Contemporary research in the area of autonomous motivation has begun to challenge the utility of aggregated measures as outlined above [*e*.*g*., 25]. Rather than being mutually exclusive or ‘either or’ constructs, it may be more relevant to investigate the particular elements of motivation as described on the continuum outlined above (Figure 2). This seems especially relevant in this case given the specific goals individuals are striving toward are not self-generated and occur in the workplace where ‘enjoyment’ is not necessarily a motivational force that is amenable or desirable as a target for change. So, we will also be able to test effects of various regulators (*i*.*e*., guilt, enjoyment, importance, fun) on the outcome variable. We will use the bootstrapping method described by Preacher and Hayes [53] to test the meditational models.

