More specifically, the literature on health behaviour change provides a foundation for understanding how to change work behaviours. It is well established within the health behaviour change literature that knowing there is ‘good evidence’ for the benefits of a specific change is a poor predictor of changed behaviour [18]. People are most highly motivated to change when the desired behaviour is something that aligns with their beliefs and values [19]. While this is true for individuals generally, it is likely to be even more salient in professions where individuals are drawn to the work for values-based reasons [20,21]. In a profession where values are central, connecting staff to the ethos in which the change is embedded is likely to be highly important to the promotion of uptake. We argue that values are persuasive in motivating staff to change their practice. In this context, we now discuss values as a key aspect of motivation.

Motivation for change is not an ‘all or nothing’ attribute. Instead, motivation can be understood in terms of the degree to which it is experienced as autonomous (arising from within the individual) or controlled (imposed on the individual by an external regulator) [22]. Within Self-Determination Theory (SDT) [22,23], striving to be self-regulated or ‘autonomous’ is described as a basic human need and something pursued by individuals. Autonomy is defined as the extent to which a behaviour is experienced as internally generated, or self-determined [24]. SDT is a well-supported theory that has underpinned a body of research related to the purposeful goal striving of individuals in a range of contexts *e*.*g*., [25,26]. Goals and behaviours that are experienced as aligned to the values and beliefs of an individual are referred to as ‘self-concordant’ [25]. The self-concordance of goals has also been shown to predict goal success, commitment to the striving process and various aspects of wellbeing [27,28].

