## Methods

### Study design and procedure

This research is informed by two previous projects undertaken by this research team, and parallels data collection time frames to enable comparisons of implementation following the addition of the new intervention component. This project is supported by an Australian Research Council grant (LP09900708), with financial and in-kind contributions by the industry partners. Partner organisations are five well-established community-managed organisations involved in the direct provision of services to individuals living with severe and recurrent mental illnesses in the community. The partner organisations will nominate a number of suitable worksites drawn from across their service base to participate in the intervention and research components. We anticipate access to teams across a number of Australian states and government areas, allowing us to compare and control for the effects of geographical variables. In total, approximately 200 mental health workers from across 22 sites will be randomised and referred for intervention.

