### Participants

Participants will be randomised by work-site to either the experimental (values) or control (implementation). Cluster-randomisation will be adopted to increase the feasibility of roll out in the organisational setting (*e*.*g*., consistency across what ‘change’ for individuals within a single worksite will look like) and minimise contamination across conditions (*i*.*e*., individual randomisation would likely lead to decreased fidelity to condition due to inevitable interactions between individual staff within teams). A computerised random integer program will be used to refer worksites to condition. Once randomised, staff from within sites will be referred for training and invited to consent to participate in the research process. Blinding will not be used at the participant or worksite level for pragmatic reasons (*i*.*e*., ongoing coaching will require condition-specific protocol) and to maximise fidelity (*i*.*e*., workers will consult with colleagues from worksites in the alternate condition during the course of duties and need to understand the importance of staying within assigned protocol). Information about previous exposure to the training (*i*.*e*., staff who have participated in some CRM training before time one) will be sought to allow screening prior to inclusion in the final data set. Staff who do not consent to participation in research but are within randomised sites will still participate in all intervention components to maximise the benefit of this project for the partners, to promote intervention fidelity within the workplace, and to allow all mental health workers access to contemporary evidence-based practices and techniques.

The intervention will be facilitated by our team and comprises both training (three days) and a 12-month coaching intervention. All teams will receive the same two days of training in the CRM [10]. On the third day of training, they will receive different training activities, according to the condition (values or implementation). In-service coaches (to be trained by our team) will conduct coaching. The in-service coaches will be supported with monthly, group-based coaching-support sessions facilitated by an appropriately skilled project member. Features of each intervention condition are as follows.

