### Data collection and handling

The study will last 18 months with data collection at multiple times points. Primary data comprises a questionnaire battery completed by participants at five time points throughout the intervention (specific measures are outlined below). Data is also collected from coaches and recipients’ at each monthly coaching session to assess adherence to the GROW framework, integrity to experimental condition, and elements of the coaching alliance. In addition to self-reported measures of implementation, the study uses objective measures of transfer (also outlined below).

Data collection handling is in accordance with the procedures specified in the ethics approval obtained from the Human Research Ethics Committee at the University of Wollongong (HE09/221). A prime focus is on maintaining confidentiality of participants, which is promoted by the use of a unique self-generated identifier established at the first data collection point and re-used at subsequent collections. Additionally, because the research focuses on work-related variables and is being conducted in a work setting, individual data is forwarded to the research team directly (*i*.*e*., handed personally in sealed envelopes when on-site). This is to reduce possible biased responding and staff concerns that their individual information could be seen by superiors or other personnel within their organisation.

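### Models B and C, as described, name no time-one autonomy or other common cause of autonomy and transfer, so a bootstrapped indirect effect can reflect staff who were already receptive and does not by itself show the mechanism

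*Protocol article*

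**What the plan says.** The Data analysis section of the protocol article sets two major questions. The second is "By what processes does the intervention work". Model A is the total effect of condition (X) on transfer (Y). For the mechanism, "Model B represents the direct effect of X on Y, and the indirect effect through the mediator (M), our psychological process variable (autonomy". Then "Model C is a multiple mediation model, and will allow us to test the extent that our intervention targets multiple process variables", and for the test of these models, "We will use the bootstrapping method". The section names no time-one value, change score or other covariate for Models B and C, and does not say which wave supplies M.

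On the design, the Participants section says "Participants will be randomised by work-site to either the experimental (values) or control (implementation", and Study design and procedure says "approximately 200 mental health workers from across 22 sites will be randomised". Only condition is therefore randomised. Data collection and handling describes a "questionnaire battery completed by participants at five time points throughout the intervention", linked by a self-generated identifier. The Background reports from earlier literature: "The self-concordance of goals has also been shown to predict goal success, commitment to the striving process and various aspects of wellbeing".

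**The concern.** A bootstrap of the product a·b (a is the effect of condition on autonomy, b the slope of transfer on autonomy given condition) asks whether condition moves autonomy and whether autonomy and transfer are associated within arm. The question of interest is whether changing autonomy changes transfer. The two coincide only if autonomy and transfer share no cause other than condition.

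Randomising sites does nothing to secure that. A worker who already finds the Collaborative Recovery Model (CRM) congenial may report more autonomy later and also use its tools more, whatever the programme does. This needs no shared questionnaire and no clustering, and it applies equally when transfer is the file audit or the count of completed tools.

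At stake is one of the two main conclusions. A programme that raises autonomy scores, without autonomy affecting practice, could be reported as working through autonomy.

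**Working it through.** The protocol gives no sample size, power or error rate for Models B and C, so there is no figure of its own to reproduce.

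**Inputs from the protocol.** About 200 workers on 22 sites; 200 expected at time one and 100 allowed for in the power calculation (Data analysis).

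**Inputs assumed.** Effect of condition on autonomy a = 0.3 to 0.5 SD; correlation r = 0.5 to 0.6 between time-one and later autonomy; correlation g = 0.3 to 0.4 between time-one autonomy and transfer; a 95% percentile bootstrap interval.

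**Step 1: the bias.** Let M0 be time-one autonomy with variance 1, and let neither autonomy nor condition affect transfer:

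- M = a·X + r·M0 + √(1−r²)·e₁
- Y = g·M0 + √(1−g²)·e₂

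Within arm, Var(M) = 1 and Cov(M, Y) = r·g, so the slope of Y on M given X is b = r·g, not 0. The indirect effect being estimated is a·r·g:

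- low end: 0.3 × 0.5 × 0.3 = 0.045
- high end: 0.5 × 0.6 × 0.4 = 0.12

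The true value is 0. With M0 in both equations, b = 0.

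**Step 2: how often the interval excludes zero.** Participant-level analysis, independent workers, 600 trials of 500 resamples per cell; unadjusted / adjusted for M0:

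| a | r, g | n=100 | n=200 |
|---|---|---|---|
| 0.3 | 0.5, 0.3 | 9% / 2% | 33% / 4% |
| 0.3 | 0.6, 0.4 | 20% / 3% | 48% / 4% |
| 0.5 | 0.5, 0.3 | 23% / 5% | 53% / 4% |
| 0.5 | 0.6, 0.4 | 47% / 5% | 91% / 6% |

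Repeat simulations gave 10% to 49% at n=100, and tops of 86% and 88% at n=200. The working range used here is about 10% to 49% and 33% to 88%. The rate rises with n because the bias does not shrink while the interval does.

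**Step 3: when the problem is small** (no site clustering unless stated).

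- a = 0, r = 0.6, g up to 0.4: 0% to 4%. At n=200 and g = 0.3 with an intracluster correlation of 0.05 to 0.10: 5% to 9%.
- g = 0: at most 6% for any a tried (up to 0.8).
- a = 0.3, r = 0.3, g = 0.2: 2% to 9% over two runs at n=100 and n=200.
- a = 0.3, r = 0.6, g = 0.2: 5% at n=100, 20% at n=200.

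**Step 4: site means.** Analysing 22 site means from the same data gave about 4% to 19% (3% to 17% in a second run). With independent workers the expected slope between site means is still r·g, so the bias is unchanged. The rate falls because 22 points estimate the slope less precisely.

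**Step 5: is the time-one term enough?** If M0 carries all the confounding, adjusted rates were 2% to 8% wherever a > 0. If a stable disposition drives M0, M and Y, and M0 is only a noisy reading of it (a = 0.5, correlation of M0 with Y of 0.2, 0.3, 0.4):

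| | Unadjusted | Adjusted |
|---|---|---|
| n=100 | 38%, 58%, 71% | 17%, 29%, 48% |
| n=200 | 75%, 93%, 96% | 30%, 61%, 88% |

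Monte Carlo error is up to about 2 points per cell.

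**The case against.** **The article condenses a fuller plan.** Covariates and mediator timing are often left to it, and Figure 2, which draws the models, is not shown. A reader might infer that the analysis has no time-one term. The documents do not support that; they show only that none is named. What remains is that the article does state the variables of Models B and C, and that set does not identify the mechanism it is meant to test.

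**The sizes are assumed.** This stands. The control is active, with the same first two training days, an experiential third day and 12 months of coaching, so a between-arm shift of 0.5 SD may be optimistic. Workers' prior CRM exposure is to be screened, so time-one answers may predict later behaviour weakly. The power calculation allows for 100 workers, so the n=200 figures may not apply. A reader might infer that the analysis will often declare autonomy the mechanism; the documents do not show this.

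**The unit may be the site.** Data analysis puts its main interest at cluster level. This stands as a reason for the lower range in Step 4, though the bias is the same there.

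**The protocol's theory says autonomy does drive implementation,** so the simulated null would be false. The theory indeed cannot serve as proof of confounding. But that theory is what the test is meant to examine, so the test must behave when it is wrong. An association between self-concordance and success is compatible with either account.

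**Conclusion.** The point holds in limited form. Models B and C as described name only condition, process variables and transfer, and randomisation leaves the autonomy-to-transfer path open to confounding. An indirect effect whose interval excludes zero would not separate autonomy driving transfer from receptive staff scoring higher on both.

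Two conditions are needed for the error to be large: the programme must move autonomy, which the authors expect, and autonomy and transfer must share a prior cause, which is plausible but not documented. Under the assumed values the false-claim rate is about 10% to 49% (n=100) or 33% to 88% (n=200) at participant level and about 4% to 19% on site means. It is near nominal when either link is absent or both are weak. None of the inputs is in the protocol, so these figures show what could happen and do not predict this trial's error rate.

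A reader might also infer that adding time-one autonomy restores the 5% level. It does so only if that measure carries all the confounding. Model A, the total effect, is not affected by this point.

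**What to change.** In Data analysis, state that:

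- the mediator equation and the outcome equation of Models B and C both include the participant's time-one value of each mediator (CRM-VQ autonomy for Model B; each process variable used in Model C), and that time one precedes study training, as the Participants section suggests but does not say outright;
- both equations also include the pre-intervention transfer measure where one exists, for example the audit of files from the six months before the intervention (time to implementation is counted from training, so it has no such value);
- the waves that supply M and Y are named, and the indirect effect is bootstrapped from these adjusted equations;
- adjustment reduces but may not remove confounding of autonomy and transfer, and the indirect effect is reported as associational unless no further common cause remains. A sensitivity analysis for unmeasured confounding would support this statement.

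Consent is sought after sites are randomised, without blinding, so time-one autonomy may differ between arms among those who consent; this is a further reason to adjust.

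The cost is a few sentences and model terms, since the battery is already repeated and linked. The downside is a few degrees of freedom, which matter more if site means are analysed, and reliance on FIML for workers with no time-one form.

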### Protocol for day three values intervention

The one-day values intervention is experiential in nature, using a structured values-clarification exercise with demonstrated utility in a range of clinical and non-clinical settings [36]. The purpose of this task is to help participants identify what values are most important to them, and to increase their awareness of the potential to actively pursue valued directions in both personal and professional domains of their life (*i*.*e*., increase the extent to which values are consciously used as a driver of purposeful behaviour). Staff members will be exposed to the concept of values in the standard CRM training (days one and two), and will have a basic theoretical and operational understanding of both the merit and applicability of working with values generally. Additionally, a focus on related concepts of willingness and commitment [37] that have been emphasised as important to values work will follow in day three.

Participants are given a set of 60 cards, each featuring a specific principle of living that is associated with a universal value-domain as outlined in Schwartz’ model [38,39]. They are then facilitated through a structured sorting task that titrates their focus down to the 15 valued directions each individual identifies as ‘most important to them.’

Following the card-sorting task, an additional intervention component is employed to foster intent and commitment to take purposeful steps toward valued areas of living. In this stage, the focus is on ‘life in general,’ and participants are asked to rate the extent to which they have purposefully been trying to enact a variety of values in the past 12 weeks. They rate their subjective success at moving toward each of the 15 specific valued directions identified as ‘most important.’ This process is structured around a worksheet based on the Personal Strivings methodology developed by Sheldon *et al*. that has been used extensively within the goal setting research [35,40].

Participants are facilitated through this process a second time, adopting a workplace focus. Participants are given the instruction; ‘conduct the card-sorting task again, this time focusing on what is most important to you in your current job.’ Following this, participants complete a second worksheet to rate the intent and self-reported success of recent striving toward the work values they have identified as most important at work.

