### Autonomy and values concordance

The Collaborative Recovery Model Values Questionnaire (CRM-VQ) is a modified version of the Personal Strivings questionnaire developed by Sheldon *et al*. [40]. The modification involves the use of perceived locus of causation from Sheldon’s strivings questionnaire, applied to the six components of CRM. This measure will examine the degree to which values embedded within the CRM are concordant with the personal values of participants. It will also assess the extent to which strivings toward the CRM practices are done for autonomous versus controlled (externally regulated) reasons.

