### Self-reported transfer

#### CRM-VQ

This measure also includes items that assess the implementation intentions and self-reported success of acting purposefully toward the valued directions encompassed within the CRM. Items include ‘to what extent have you made specific plans about when, where, and how to put this value into play?’ and ‘In the last 12 weeks, I have been this successful in living this value,’ to which responses will be elicited on a five-point Likert scale. An additional item relating to anticipation of implementation barriers (‘to what extent have you anticipated possible distractions and obstacles to putting this value into play?’) has been included and will be rated in the same manner. This item will allow us to investigate the impact of deliberately addressing implementation barriers (control condition).

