### Qualitative assessment of concordance between work samples and CRM values

A novel aspect of this research is the utilisation of a process-oriented protocol to assess worker adherence to the principles embedded within CRM. For example, the principle of personalisation (*i*.*e*., evidence of unique and person-centred approach to service delivery) is acknowledged as important in recovery [3]. Personalisation will be assessed across two dimensions (the content in the sample reflects unique expression of ideas; the language/presentation of content reflects individuality) using a three-point scale (0 = no, 1 = partially, 2 = yes). De-identified research copies of work samples are to be forwarded by participating mental health workers on a monthly basis by an on-site coordinator. Following power calculations, an online number generator will be used to facilitate random identification of an appropriate number of staff whose work-samples are to be reviewed. The samples of randomly identified staff will be reviewed using the six-point rating system at three time points (one month post-training, six months post-training, and 12 months post-training). Two trained assessors from within the research team will independently review the work samples for worker process and satisfactory inter-rater reliability will be established. We will compare observed adherence to CRM principles with the self-reported transfer and measures of autonomy obtained via the CRM-VQ (described above) at matching time periods (*i*.*e*., six and 12 months) during booster sessions to explore these differing elements of implementation.

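### With self-reported transfer as the outcome, Model C lists that outcome among its mediators and Model B takes mediator and outcome from one questionnaire, so an indirect effect need not show mechanism

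*Protocol article*

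**What the plan says.** All references are to the protocol article.

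- **Outcome of the mediation models (Data analysis).** "Model A represents the total effect of values intervention versus control condition (implementation) (X) on Transfer (Y"). Which transfer measure serves as Y is not stated.
- **Mediators (Data analysis).** Model B estimates "the indirect effect through the mediator (M), our psychological process variable (autonomy"). Model C has several process variables, for example "value importance, value success, value commitment". The indirect effects are to be tested by bootstrap.
- **Success as an outcome (the CRM-VQ subsection under Self-reported transfer).** The questionnaire has a second role there: "This measure also includes items that assess the implementation intentions and self-reported success of acting purposefully toward the valued directions encompassed within the CRM". The success item asks about the last 12 weeks on a five-point scale.
- **Source of the autonomy score (Autonomy and values concordance).** The CRM-VQ, a modified Personal Strivings questionnaire, supplies it: "It will also assess the extent to which strivings toward the CRM practices are done for autonomous versus controlled (externally regulated) reasons".
- **Exposure of the values arm only (Protocol for day three values intervention).** Participants rate their intent and success on their own values: "This process is structured around a worksheet based on the Personal Strivings methodology". The control arm spends day three on a SWOT analysis.
- **Blinding (Participants).** None at participant or worksite level.
- **Other transfer measures.** The article also plans LifeJET documents in files, a 17-element file audit and rated work samples.

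**The concern.** One of the two major questions in the Data analysis section is by what processes the intervention works, and Models B and C are meant to answer it. There are two separate difficulties, both confined to self-reported transfer as Y.

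1. **Circularity in Model C.** The CRM-VQ is the only described measure of value success taken in both arms. The article files it under self-reported transfer and also names it as a mediator of transfer. Regressing success on success returns an indirect effect whatever the mechanism.
2. **Same source in Model B.** Autonomy and self-reported transfer are answered on one form by staff who know their condition. Only the values arm has completed worksheets from the methodology on which that form is built. If the training changes how that arm uses the scales, both M and Y move, and the bootstrap can report mediation with no change in motivation or practice.

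Randomisation protects the X-to-M and X-to-Y contrasts from confounding. It does not protect the M-to-Y path.

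**Working it through.** The article gives no sample size, power or effect size for the mediation test, so there is no stated figure to reproduce. From the article: about 200 workers, 22 sites, and 100 as the cautious sample size. Everything else below is an assumption. The test is taken as a two-sided 95% percentile bootstrap interval for a×b.

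**Step 1. Value success as both M and Y.** Let T be true success, with X moving T by 0.4 SD (assumed) and var(T)=1 within arm. Let M and Y be two readings of T, each with reliability ρ.
- a = 0.4; total effect = 0.4; b = var(T)/var(M) = ρ.
- Indirect/total = 0.4×ρ/0.4 = ρ.
- Same item (ρ=1): 100%. ρ=0.8: 80% (simulated 81%). ρ=0.6: 60% (simulated 60%).

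This needs no assumption about reporting style.

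**Step 2. Autonomy and self-reported transfer on one form, no true effect on either.** Let M = S + e₁ and Y = S + e₂, where S is reporting style with variance 0.36 (SD 0.6), each error has variance 0.64, and the observed scale has SD 1. Values training shifts S and nothing else.
- b = 0.36/(0.36+0.64) = 0.36; a = the shift in scale units; indirect effect = 0.36×shift.

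The unit of the shift matters, because 1 SD of style is only 0.6 SD of the observed scale:

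| Shift of 0.2-0.5 SD, in units of | In scale SD | Indirect effect | False mediation, n=100 | n=200 |
|---|---|---|---|---|
| style | 0.12-0.30 | 0.04-0.11 | about 8-32% | about 15-59% |
| observed scale (0.33-0.83 SD of style) | 0.20-0.50 | 0.07-0.18 | about 15-70% | about 28-94% |
| no shift | 0 | 0 | about 5-7% | about 5-7% |

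A repeat of this simulation (1,000 trials per cell, 400 resamples) agreed within simulation error: 8% to 33% at n=100 and 15% to 58% at n=200 for the style-unit shift, 16% to 66% and 32% to 96% for the scale-unit shift, and 5% with no shift.

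**Step 3. The training does move autonomy, but autonomy does not affect practice.** The values arm is designed to move M, so this case needs no arm difference in style. With X moving M by 0.5 SD and style producing a correlation r between M and Y (500 trials per cell, 22 sites split 11:11, intracluster correlation zero):

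| r | n=100 | n=200 |
|---|---|---|
| 0.1 | 13% | 24% |
| 0.3 | 57% | 93% |
| 0.5 | 71% | 93% |
| 0 (Y from a separate source) | 4.8% | 3.8% |

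The last row shows what a separate-source outcome buys: the error rate returns to nominal.

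**The case against.** **The models define Y as Transfer, not as self-reported transfer.** This stands. LifeJET use, the file audit and the rated work samples do not share the CRM-VQ, and mediation on them is untouched by this point. A reader might infer that Models B and C are invalid altogether, and the article does not support that. Nor does it confine the mediation to those measures.

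**Nothing fixes mediator and outcome at the same wave.** This also stands. A reader might infer simultaneity from the work-sample section, which says "We will compare observed adherence to CRM principles with the self-reported transfer and measures of autonomy obtained via the CRM-VQ" at matching six- and 12-month periods. That sentence describes a check of rated work samples against questionnaire scores. It does not choose waves for Models B and C. The battery is given five times, so a lag is possible, and the choice of wave may be left to a fuller plan. It is not counted as an error here.

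**The Step 2 bias needs an arm difference in reporting style, for which the article gives no figure.** True. Both arms meet values on days one and two, use CRM tools in coaching and complete the same battery. Without a shift and without an effect on M, the error rate is near nominal. However, Step 3 needs no such shift, and Step 1 needs no style at all.

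**Value success appears only as an example in one multiple-mediator model.** True, and it makes the correction easy. It does not remove the overlap.

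**Conclusion.** The point holds for self-reported transfer as Y. Value success then stands on both sides of Model C, and between 60% and 100% of the total effect appears as indirect for reliabilities from 0.6 to 1. For Model B the risk is shared reporting style. Its direction follows from the design; its size rests on assumptions. With a 36% style share and a 0.2-0.5 SD shift of style, false mediation occurs in about 8-32% of trials at n=100 and 15-59% at n=200.

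Rates as high as 70% and 94% in the no-true-effect case should not be quoted for a 0.5 SD shift of style. They need a shift of 0.5 SD of the observed scale, which is 0.83 SD of style.

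The conclusion does not extend to the objective transfer measures, and it does not assert that M and Y are taken at one wave. It is worth correcting before analysis because it bears on one of the two major questions and the change is one of wording.

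**What to change.** In the Data analysis section:

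1. Remove value success from the mediators whenever self-reported transfer is Y, and keep it as an outcome.
2. Name a file-based transfer measure, either LifeJET use or the file audit, as Y for the main mediation test. This is the key change.
3. Take autonomy from an earlier wave than Y, adjusted for its time-one value. Six-month autonomy with the audit's six-to-twelve-month period would fit the existing schedule. If LifeJET is chosen, use evidence from after the autonomy wave, because first use may come before it.
4. Report mediation with both M and Y from the CRM-VQ as supportive only.

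A lag by itself is not enough, because a stable response style persists across waves. A separate source and a lag still leave ordinary confounding of the M-to-Y path, so the result should be worded accordingly.

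Cost: no new measures. Some precision is lost to later attrition, and more if the rated work samples are used, since these cover only a random subset of staff. File evidence must be linked to questionnaires held under a self-generated identifier, so that link should be confirmed for the chosen Y.
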